### Analysis plan

Data will be coded, entered, and analyzed using the Statistical Package for Social Science (SPSS) version 20.0 for Windows (SPSS, Chicago, Illinois, USA). We will describe continuous variables using means with standard deviations, and categorical variables using their frequencies and percentages. We will use the principle of ‘intention to treat’ analysis. The risk ratio will be used to measure effect of interventions on proportion of presence at medicals appointments and will be expressed with 95% confidence interval. The *t*-test will be used to compare quantitative variables, and the chi-square test will be used to compare qualitative variables. A *P* value less than 0.05 will be considered statistically significant. WinPepi will be used to measure the interaction between SMS and call in the group receiving both call back methods of appointment.

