**Methods/Design:**

We will carry out a multicenter single-blind, randomized, factorial controlled trial. A randomization list will be electronically generated using random block sizes. Central allocation will be determined by sequentially numbered. A total of 224 subjects will be randomized into four groups (SMS, Call, SMS + Call, and Control) with an allocation ratio of 1:1:1:1. SMS and calls will be sent between 48 and 72 hours before the scheduled appointment. A medical assistant will send out text messages and will call participants. Our primary outcome is appointment measured by efficacy and efficiency of interventions. We hypothesize that two reminders (concomitant use of SMS and phone calls) as an appointment reminder is more effective to improve appointment compared to one reminder (only SMS or only call), and that the most efficient is use of only SMS. The analysis will be intention to treat.

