### Trial design

We will carry out a 2 x 2 factorial, multicenter randomized controlled trial, single-blind with an allocation ratio of 1:1:1:1 for adult-child pairs to four groups. Group 1 will serve as the control group and is composed of subjects provided an appointment and no reminder, reflecting the usual standard of care. Group 2 subjects will be provided an appointment and an SMS reminder. Group 3 members will be provided an appointment and a voice phone call reminder. Group 4 members will be provided both an SMS and a voice phone call reminder. A schematic of the groups and a study diagram according to the recommendations of the Consolidated Standards of Reporting Trials (CONSORT) [19] are shown in Figures 1 and 2 respectively. The study will be performed for 5 months, from January to May 2013.

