### Randomization

Randomization assignments will be generated in blocks of four for each study site and will be allocated electronically using WinPepi version 11.25 [20]. After data collection of eligible subjects (adult-child pairs) who have given their consent, we will randomly assign participants into four groups. Allocation and randomization will be made centrally. In each block that is randomly pre-constituted, each subject (adult-child pair) will be allocated to one group.

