**Primary**				
Presence at appointment				
• Efficacy	Nominal	Binary	% present at appointment	Chi-square test
				Additive and multiplicative scales for synergy measurement
• Efficiency	Ratio	Continuous	Mean of efficiency	*T*-test
- Working time	Ratio	Continuous	Mean of working time	*T*-test
- Financial cost	Ratio	Continuous	Mean of financial cost	*T*-test

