#### Sample size

The primary objective is to measure the patient presence at their scheduled appointment. The calculation of the sample size will be based on the comparison of proportions of presence at appointment. The value of alpha is 0.05. The test is two-tailed. We assume that the presence at appointments using SMS as reminder and phone calls is, respectively, 59.0% and 59.6% [11]. We also assume that the difference would be 25% between the group that will receive both SMS and phone calls and the groups that will receive only an SMS or only phone calls. The minimum size of the sample required will be 50 subjects in each group for analysis by intention to treat with 80% power and a significance level of 0.05. We will exclude from analysis the participants with incomplete data. For this we assume a 10% attrition rate. Thus, we will need 224 subjects (56 in each group). WinPepi has been used to calculate the size of the sample [20].

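### Allocation is blocked within site, but attendance is analysed without site: conservative, and mildly wasteful of power if attendance differs materially between sites

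*Protocol article*

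**What the plan says.** - **Allocation.** Protocol article, Randomization: "Randomization assignments will be generated in blocks of four for each study site". Trial design describes the trial as "single-blind with an allocation ratio of 1:1:1:1 for adult-child pairs to four groups". The abstract words the blocking differently ("A randomization list will be electronically generated using random block sizes"). That discrepancy does not matter here, because either scheme run by site balances the arms within site.
- **Primary analysis.** Table 1 gives the attendance entry as "present at appointment Chi-square test". The Analysis plan repeats this in general terms ("the chi-square test will be used to compare qualitative variables") and sets the effect measure: "The risk ratio will be used to measure effect of interventions on proportion of presence at medicals appointments", with a 95% confidence interval. Neither place names site, strata or covariates.
- **Where setting is used.** The three settings are compared only under Additional studies, for phone ownership, means of communication and refusal.
- **Error rate.** Sample size: "The value of alpha is 0.05" and "The test is two-tailed".

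**The concern.** When arms are balanced within site, differences in attendance between sites largely cancel out of the comparison between arms. A plain chi-square test and an unadjusted risk ratio still count that between-site variation in their variance. If site predicts attendance, the reported standard error exceeds the true one, the p value tends to be too large and the interval too wide.

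A site effect is plausible. The protocol chose an urban, a semi-urban and a rural hospital and describes their populations as socioeconomically and demographically different. Its Background lists transport cost and clinic location among the reasons for missed visits. At stake is precision that the design has already secured and the analysis does not use.

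**Working it through.** **1. The plan's own figure.** Inputs from Sample size: 59.0% (SMS) or 59.6% (call), a 25-point difference, two-sided alpha 0.05, 80% power.

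n = [1.96 × √(2p̄(1−p̄)) + 0.8416 × √(p₁(1−p₁) + p₂(1−p₂))]² / (p₂−p₁)²

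With p₁ = 0.59, p₂ = 0.84 and p̄ = 0.715, n = [1.96 × √0.40755 + 0.8416 × √0.3763]² / 0.0625 = 49.99, so 50. Starting from 59.6%, n = 49.3, again 50. Then 50/0.9 = 55.6, so 56, and 4 × 56 = 224. The stated figures reproduce with an unstratified formula.

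**2. How much too wide is the standard error?** Under no treatment effect the plain test uses the total variance P(1−P), where P = Σwᵢpᵢ. With balance within site the true variance is the within-site part, Σwᵢpᵢ(1−pᵢ). The ratio of standard errors is R = √(total/within), and the actual type I error is about Pr(|Z| > 1.96R). Site shares of 25/15/10 per arm are assumed.

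| Assumed site attendance | Total variance | Within-site variance | R | Approx. type I error |
|---|---|---|---|---|
| 65/55/50% | 0.59 × 0.41 = 0.2419 | 0.2380 | 1.008 | 4.8% |
| 75/55/40% | 0.62 × 0.38 = 0.2356 | 0.2160 | 1.044 | 4.1% |
| 85/50/25% | 0.625 × 0.375 = 0.2344 | 0.1763 | 1.153 | 2.4% |

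Example for 75/55/40%: 0.5 × 0.1875 + 0.3 × 0.2475 + 0.2 × 0.24 = 0.2160. Simulation with 28/17/11 per arm agrees: about 4.0% for 75/55/40% and 2.3% for 85/50/25%, against 5.0% for the Cochran-Mantel-Haenszel (CMH) test in both.

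**3. Power at the planned effect.** Simulation with 50 per arm, a common log-odds shift giving a 25-point overall gain, and no continuity correction:
- 65/55/50%: about 81% for both tests.
- 75/55/40%: about 85% plain, 86% stratified.
- 85/50/25%: about 87% plain, 91% stratified.

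The last two have a starting rate of about 62% rather than 59%, which partly explains why even the plain test exceeds 80%.

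**4. The same check at the protocol's own rates.** Overall attendance fixed at 59% v 84%, 50 per arm, assumed site shares 60/25/15%, 40,000 runs per row:

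| One-reminder attendance by site | Power, plain | Power, CMH | Type I error, plain | Type I error, CMH |
|---|---|---|---|---|
| 59/59/59% | 81.1% | 80.8% | 5.3% | 5.3% |
| 56/63/63% | 80.7% | 80.5% | 5.1% | 5.2% |
| 66/54/41% | 81.6% | 82.1% | 4.8% | 4.9% |
| 72/49/26% | 82.2% | 85.1% | 3.8% | 4.8% |
| 77/43/14% | 84.1% | 89.9% | 2.5% | 4.9% |

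In the 72/49/26% row, the average unadjusted standard error of the difference under the null is 0.0975 against a true sampling SD of 0.0920, so it is 6% too wide (0.0975/0.0920 = 1.06). Equal site shares give the same pattern.

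**The case against.** The case against has real force on size.

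- **Evidence for a large site effect is thin.** The only related figure in the protocol is six-week loss to follow-up, 17.0% in the Centre region and 13.3% in the Far North, a gap of 3.7 points. It is indirect: it is not appointment attendance, and it cannot separate the two Far North sites. The 56/63/63% row has a spread somewhat larger than that gap, and there stratifying gains nothing.
- **A reader might infer a large power loss.** Adding a flat 20 points to sites at 85/50/25% appears to cost 12 points of power (52% v 64%). That scenario needs 105% attendance at the first site. Capping it cuts the overall gain to about 17 points, so much of the low power reflects a smaller effect. A feasible shift giving a true 20-point gain with 56 per arm yields 69% v 77%, and that is still below the planned effect.
- **A reader might infer an invalid or underpowered trial.** The documents do not support that. The error is conservative, balanced arms leave the unadjusted risk ratio unbiased by site, and the plain test keeps at least 80% power at the design effect in every scenario above.
- **Covariate adjustment is often left to the analysis plan.** That is true, and the Analysis plan paragraph is brief. But Table 1 does assign a specific test to the primary outcome, so the mismatch lies in what the protocol states, not in what it leaves out.

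**Conclusion.** The point holds as a mismatch between design and analysis with a modest, conditional cost. If attendance differs materially by site, the plain test is conservative (about 4.0% at 75/55/40%, about 2.3% at 85/50/25%) and gives up about 1 and 4 points of power respectively at the planned 25-point effect with 50 per arm. The most extreme spread tried, 77/43/14%, costs about 6 points (89.9% v 84.1%). Small site differences cost essentially nothing.

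The direction follows from the stated randomisation. The size rests on assumed site rates and site shares, and on near-complete balance within site. The sample size and the planned power are unaffected.

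**What to change.** Before the group codes are broken, state that attendance will be compared by a CMH test stratified by the three sites, with a Mantel-Haenszel risk ratio and 95% confidence interval. A risk-ratio model (log-binomial or modified Poisson) with site as a fixed effect is an acceptable alternative. Include site in the SMS-by-call interaction analysis as well, and keep the plain chi-square test and unadjusted risk ratio as a sensitivity analysis. Amend Table 1 and the Analysis plan together so that they agree.

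The cost is wording. Site is already known for every participant because the allocation uses it, and no extra data or participants are needed. If site turns out not to matter, the price is negligible (80.8% v 81.1% power with no site difference).

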## Background

In Central Africa, vertical transmission of human immunodeficiency virus (HIV) infection from mother to child approaches 30%, reflecting in part inadequate implementation of postnatal preventive strategies, especially during breastfeeding [1]. In Cameroon, the number of new pediatric HIV infections was increasing and reached 6,800 in 2011 [2]. Recent estimates indicate that only 13% of children requiring antiretroviral HIV therapy (ART) actually receive it [2]. Inadequate attendance at medical follow-up visits in infancy is a potentially reversible factor. Only 65% of infants born to seropositive mothers presented to the recommended six-weeks-of-age medical visit [3]. Many factors underlie nonattendance at scheduled visits for HIV care and loss to medical follow-up. These include intrapersonal factors such as the cost of transportation, food availability, time constraints due to concomitant work, fear of disclosure of HIV status for mother and child, parental perception that the child is healthy, and personal religious beliefs. Interpersonal factors like male partner nonparticipation, familial stigmatization and conflicts play a role as well. Community factors include accepted cultural norms, changing community dynamics, and perceived stigma; these factors, along with health care system factors such as the clinic location, lack of patient-centered care, delays at the clinic, and different appointment scheduling for mother and child contribute to non-adherence with medical visits [4].

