### Blinding

The treating physician, the medical administrative assistant who will contact participants in Groups 2, 3, and 4 via mobile phone, the nurse (outcome assessor) responsible for recording patient presence or absence at the appointment, and analysts will be blinded. The participant will be received at the reception, and after giving his/her written consent, data will be collected by a nurse. The nurse will then send the following information to the medical administrative assistant: the identification code of the participant, date of appointment, the physician’s name, the phone number of the participant and the language of communication (French or English). A medical administrative assistant will then be responsible for carrying out all intervention: the sending of SMS and the calls to participants. The appointment will then be notified by the nurse of the reception. Before data analysis, we will assign a code for the four groups.

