### Participants

We will include in the study all persons aged 18 years or older accompanying a HIV-infected or exposed child aged less than 15 years for HIV care and consenting to participate in the study. We will exclude to randomization i) subjects who do not have a mobile phone; ii) subjects whose follow-up appointment is scheduled in less than 3 days; and iii) subjects who are unable to communicate, read, or write in English or French.

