Compared to SMS, which is not interactive, a phone call is a better channel for message delivery to patients or their close relatives. On the other hand, unlike a phone call, in using SMS, if the recipient is not immediately reachable when the message is sent, he/she can read the text message afterwards. In addition, in Africa, some barriers like timing of messages, mobile network fluctuations, and mobile phone turnover can reduce the potential use of mobile phone technology to improve adherence to treatment [24]. Other barriers include language impediments and lack of financial incentive.

Some factors associated with non-adherence to ART in the adult population in Cameroon can influence presence at appointment: high monthly income, binge drinking, drug and tobacco use, lack of family support for adherence, potential for experiencing discrimination and stigma, switching regimen, increased duration on medication, cost of care, increased distance from clinic, large hospital size, and no task shifting from physician to other staff [25]. In some previous studies, the sending of SMS was the less financial cost method compared to voice phone call [17]. The use of mobile phone reminder in this trial can reduce impact of some correlates of nonattendance to medical appointments in Cameroon.

Finally, the study will possibly contribute to increasing evidence of the usefulness of mobile phone technology for promoting health in low- to middle-income countries like Cameroon [26].

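### The primary attendance analysis is fixed as unadjusted, although site, the child's HIV status and days to the appointment are known before randomisation; adjusting for them costs nothing and may add a little power

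*Protocol article*

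**What the plan says.** The Analysis plan states that "the chi-square test will be used to compare qualitative variables" and gives the effect on attendance as a risk ratio with a 95% confidence interval. The efficacy row of Table 1 assigns the chi-square test to this outcome, with additive and multiplicative interaction measures. Neither place names a baseline variable.

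The design sections show what is known before assignment:

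- **Site.** The Randomization section blocks assignments in fours within each study site.
- **Child's HIV status.** The Participants section enrols adults "accompanying a HIV-infected or exposed child aged less than 15 years", so the eligibility check involves the child's status.
- **Days to the appointment.** The same section excludes pairs whose appointment is less than 3 days away. The Blinding section has the nurse pass on "the identification code of the participant, date of appointment" and other items.

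The Randomization section places data collection before assignment.

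**The concern.** The trial pools HIV-infected and HIV-exposed children, with lead times that may vary widely, and randomises within site only. If any of these variables predicts attendance, an unadjusted comparison leaves that variation in the error term and leaves chance imbalance uncorrected.

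The protocol gives some reason to expect prediction. The Background lists "parental perception that the child is healthy" among the causes of missed visits, which could differ between exposed and infected children. The Discussion names "switching regimen, increased duration on medication" among factors that may affect attendance. The reminders target forgetting, which plausibly grows with lead time. Six-week loss to follow-up is given as 17.0% in the Centre region and 13.3% in the Far North.

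At stake is some power for the planned contrast of SMS + call with a single reminder, obtainable from the same pairs and data.

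**Working it through.** **Inputs from the Sample size section.** "The value of alpha is 0.05"; "The test is two-tailed"; "50 subjects in each group for analysis by intention to treat with 80% power and a significance level of 0.05". Attendance is 59.0% with SMS and 59.6% with a call. The combined arm is 25 points higher, and attrition is 10%.

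**Step 1: reproduce the plan's figure.** For 59% v 84% the mean is 0.715. With pooled variance under the null:

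n = [1.960 × √(2 × 0.715 × 0.285) + 0.842 × √(0.59 × 0.41 + 0.84 × 0.16)]² / 0.25²
= (1.251 + 0.516)² / 0.0625 ≈ 50.

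The pair 59.6% v 84.6% also gives 50. Then 50 / 0.9 = 55.6, rounded up to 56, and 4 × 56 = 224. The plan's numbers are right for the crude test.

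**Step 2: approximate effect of adjustment.** If baseline variables explain a share R² of the outcome variance, the effective size per group is about 50 / (1 − R²). The documents give no R², so it is varied.

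| Assumed R² | Effective n per group | Power |
|---|---|---|
| 0 | 50.0 | 80.0% |
| 0.02 | 51.0 | 80.8% |
| 0.05 | 52.6 | 82.0% |
| 0.10 | 55.6 | 84.1% |
| 0.15 | 58.8 | 86.1% |

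**Step 3: simulation.** Each setting has 50 per arm and 59% v 84% attendance. Half the children are infected (assumed), lead time is standardised, and site is not modelled. Odds ratios are for HIV status and per SD of lead time. There were 4,000 to 6,000 trials per setting, so the Monte Carlo SE of each power is about 0.5–0.6 points.

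| Adjusted method | Assumed strength | Chi-square | Adjusted | Change |
|---|---|---|---|---|
| Logistic, likelihood-ratio test | none | 80.9 | 80.8 | −0.1 |
| | R² about 3% | 80.6 | 82.0 | +1.4 |
| | R² about 9% | 81.5 | 84.8 | +3.3 |
| | R² about 15% | 80.4 | 86.3 | +5.9 |
| Logistic, score test | none | 81.5 | 81.5 | 0.0 |
| | OR 1.5 and 1.3 | 81.5 | 81.6 | +0.1 |
| | OR 2 and 1.5 | 81.3 | 83.0 | +1.7 |
| | OR 3 and 2 | 81.0 | 85.9 | +4.9 |
| Modified Poisson, robust SE | none | 81.2 | 79.9 | −1.3 |
| | OR 1.8 and 1.3 | 80.8 | 80.3 | −0.5 |
| | OR 3.0 and 1.6 | 80.4 | 82.4 | +2.0 |
| | OR 3.9 and 2.2 | 80.0 | 84.1 | +4.1 |

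A further run of both models, with the chi-square at about 81% throughout, gave 82, 82, 84 and 87% for adjusted logistic and 80, 81, 82 and 85% for modified Poisson (none, weak, moderate, strong). The crude risk-ratio test itself has 79–80% power. The small deficit of modified Poisson when nothing is prognostic therefore comes from testing a risk ratio by its standard error instead of by chi-square, not from the covariates.

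Type I error was about 5–6% for the adjusted tests. The highest value was 6.3%, for the logistic score test with strong covariates, against 5.5% for the chi-square test in the same setting. A little of the largest logistic gain may reflect that difference.

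**Step 4: chance imbalance.** With half the children infected, the between-arm difference in infected share has SD √(2 × 0.5 × 0.5 / 50) = 0.10, ignoring any balance from site blocking. If attendance differs by 22 points between the two statuses (assumed), a one-SD imbalance moves the crude contrast by 0.10 × 22 = 2.2 points. The standard error of that contrast is √[(0.59 × 0.41 + 0.84 × 0.16) / 50] = 8.7 points, so the shift is modest.

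**The case against.** The strongest reply is that nothing is wrong: the chi-square test is valid, chance imbalance is already covered by its type I error, and the sample size was built on it. All of that stands. A reader might infer that the crude analysis is biased, or that the trial is underpowered because of it. Step 1 shows the planned 80% is met under the plan's own inputs.

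A reader might also infer that power is definitely being thrown away. The documents do not support that, for these reasons:

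- They give no figure for how HIV status or lead time relates to attendance.
- The Discussion's list describes adults' non-adherence to antiretroviral therapy, not children's clinic visits.
- The Background does not tie the perceived-health factor to infected v exposed status, and no section relates lead time to attendance.
- The regional figures differ by only 3.7 points and concern six-week follow-up.

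With weak predictors the gain is close to nil, and for modified Poisson it is within simulation error of zero.

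HIV status also needs care. Some exposed children will not yet have a diagnosis, and the article does not state outright that the infected/exposed distinction is recorded. It follows only from the eligibility wording. The variable must therefore be the classification at enrolment.

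A statistical analysis plan that is not shown could add an adjusted analysis. That does not remove the point, because the article itself names the unadjusted test as the method for the primary outcome.

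**Conclusion.** The point holds as an optional, low-priority improvement. The primary attendance analysis is fixed as unadjusted while three usable baseline variables are available before assignment. Site has the firmest claim, since it is the only factor on which randomisation is blocked.

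For HIV status and lead time together, the change in power at 50 per group is about 0–1 point if they are weak predictors, 1–3 if moderate and 4–6 if strong. The downside is about 0–1.5 points against the chi-square test if neither is prognostic. These ranges rest on an assumed 50% infected and on assumed predictor strengths. They do not include any effect of site. The logistic figures are for the test of arm in the adjusted model, not for the confidence interval of a standardised risk ratio.

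**What to change.** In the Analysis plan and the efficacy row of Table 1, state that the primary risk ratio and 95% confidence interval for each planned comparison come from a prespecified model. Its terms are arm, site, the child's HIV status as classified at enrolment (infected v exposed) and days to the appointment. Use either logistic regression standardised to a marginal risk ratio or modified Poisson regression with robust standard errors, and name one in advance. Either keeps the risk ratio already planned. Retain the crude chi-square test as a sensitivity analysis.

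The cost is a sentence or two and one regression model, with no further pairs or visits. No new data are needed provided the infected/exposed classification is written down at enrolment. The Trial status section reports recruitment as ongoing and analysts are to be blinded, so the model can be fixed before anyone sees results by group.

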### Outcome measures

#### Primary outcomes

Table 1 shows an overview of the outcomes and statistical method that will be used. The primary outcome will be the presence at appointment. It will be measured by effectiveness, and efficiency related to both financial cost and working time. Effectiveness will be the capability of producing a presence at an appointment (attendance). We will measure three aspects of efficiency using the following ratios: i) presence at appointment/financial cost x working time; ii) presence at appointment/financial cost; and iii) presence at appointment/working time. Time for text message intervention will be measured from the start of writing the message until the sending. For phone calls, this time measure will begin when we make the first call (not when the participant picks up the phone) and will stop at the end of the communication. The cost of each call and SMS will be evaluated using a prepaid plan. The prepaid plan means that the phone will have a financial amount of communication known before the call. After call, the difference will be made with the remaining amounts. Each SMS will cost 50 or 100 Francs of Financial Community of Africa (FCFA) (approximately 0.076 € or 0.152 €).

**Table 1 T1:** Overview of outcome measures

**Outcomes measures**	**Scale**	**Type**	**Measure**	**Analysis method**

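### The sample size is for one two-arm comparison, but the hypothesis sets SMS + Call against two single-reminder groups with no success rule, and attendance shares the primary tier with efficiency, time and cost

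*Protocol article*

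**What the plan says.** All of this is in the protocol article.

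- **Hypothesis (Abstract, Methods/Design).** Two reminders together are expected to be "more effective to improve appointment compared to one reminder (only SMS or only call").
- **Sample size.** "The value of alpha is 0.05" and "The test is two-tailed". On the single-reminder rates: "We assume that the presence at appointments using SMS as reminder and phone calls is, respectively, 59.0% and 59.6"%. On the effect: "We also assume that the difference would be 25% between the group that will receive both SMS and phone calls". The comparator is given in the plural, as "the groups that will receive only an SMS or only phone calls". The result is 50 per group at 80% power, raised to 56 per group (224 in total) for 10% attrition. This section also names presence at the appointment as the primary objective.
- **Primary outcomes and Table 1.** Of presence at appointment, the article says: "It will be measured by effectiveness, and efficiency related to both financial cost and working time". Three efficiency ratios are defined. Table 1 lists efficacy, efficiency, working time and financial cost under Primary, with a chi-square test for the first and t-tests for the others.
- **Analysis plan.** Chi-square and t-tests are named, and a P "value less than 0.05 will be considered statistically significant".

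The article does not say whether the two-versus-one hypothesis succeeds on one contrast, on both, or on the two single-reminder groups combined.

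**The concern.** One sample size, one alpha and one power are attached to a hypothesis with two comparisons that share the SMS + Call arm. Suppose SMS + Call beats Call only but not SMS only. The article does not say whether the trial has then shown that two reminders beat one. The answer determines both the error rate and the power. Counting either win inflates the error above the stated level, and requiring both lowers the power below the stated 80%.

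Placing efficiency, working time and cost beside attendance in the primary tier makes this worse, because a significant t-test on one of them could also be reported as a primary result. The trial was not sized for those measures.

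**Working it through.** **Inputs (Sample size section).** Two-sided alpha 0.05; power 80%; SMS only 59.0%; Call only 59.6%; difference 25 points, so SMS + Call is 84.0% (59.0 + 25) to 84.6% (59.6 + 25); 50 evaluable per group, 56 randomized.

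**1. Reproduce the stated size.** Pooled-variance formula without continuity correction, with p̄ = (p1 + p2)/2:

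n = [1.960·√(2p̄(1−p̄)) + 0.842·√(p1(1−p1) + p2(1−p2))]² / (p2 − p1)²

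- 59.0% v 84.0%: (1.2512 + 0.5163)² / 0.25² = 49.99, so 50.
- 59.6% v 84.6%: (1.2432 + 0.5127)² / 0.25² = 49.3, so 50.
- Attrition: 50/0.90 = 55.6, so 56; 4 × 56 = 224.

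The stated 50, 56 and 224 reproduce, for a single two-arm comparison at the full 0.05.

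**2. Success on either contrast.** Simulated with all arms at 59%, using the uncorrected two-proportion z-test (equivalent to the chi-square test):

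| Event under no difference | 50 per arm | 56 per arm |
|---|---|---|
| One given contrast significant, two-sided | 5.3% | 4.7% |
| At least one of the two significant, two-sided | 9.6% | 8.5% |
| SMS + Call declared better in one given contrast | 2.7% | 2.4% |
| SMS + Call declared better in at least one | 4.8% | 4.2% |

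For comparison, the either-contrast two-sided figure is 9.1% under a bivariate normal with correlation 0.5 (the shared arm) and 1 − 0.95² = 9.75% under independence.

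**3. Success on both contrasts.** Simulated with SMS at 59.0% and Call at 59.6%, each contrast tested at two-sided 0.05:

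| SMS + Call rate | n per arm | v SMS | v Call | Both |
|---|---|---|---|---|
| 84.0% | 50 | 81% | 79% | 69% |
| 84.6% | 50 | 83% | 81% | 72% |
| 84.0% | 56 | 85% | 83% | 74% |
| 84.6% | 56 | 87% | 86% | 77% |

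A normal approximation gives slightly lower joint power at 50 per arm, 66-69%.

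**4. One pooled contrast.** Group 4 (50) against Groups 2 and 3 combined (100), with the combined rate (59.0 + 59.6)/2 = 59.3%. Power is 89% by formula and 90% by simulation with SMS + Call at 84.0%, and 91% by either method at 84.6%. The simulated two-sided level is about 5.3%.

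**5. What the pooled contrast can miss.** If SMS + Call and SMS only are both 84% and Call only is 59%, the combined single-reminder rate is (84 + 59)/2 = 71.5%. The pooled test is then significant in favour of SMS + Call in about 40% of trials at 50 v 100, although adding a call to the SMS brings nothing.

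**The case against.** - **The 80% is correct for each contrast.** If the two comparisons are separate claims, each has about 80% power at a nominal 5%. This stands, so the sample size calculation is not itself wrong. The defect is that the article states a joint hypothesis without saying how the two tests combine.
- **The hypothesis may mean an average.** It can be read as two reminders against one reminder of either kind. On that reading the trial has about 90% power and 80% is conservative. The wording allows this, but the Sample size section treats the single-reminder groups separately, with two rates, and names no pooled test.
- **A reader might infer a 10% chance of a false claim that two reminders beat one.** The documents do not support that. The 9.6% counts significance in either direction, including SMS + Call being worse. A false claim of superiority over at least one arm has a chance of about 4.8%, roughly double the nominal 2.5%.
- **A reader might infer that all pairs of arms are tested, and that the synergy scales add further tests at 0.05.** The article names the types of test but not all pairs. It describes the additive and multiplicative scales, and the WinPepi interaction, as measurement, with no stated P-value test. Neither inference is part of this point.
- **A reader might infer that the outcomes have no ranking at all.** That goes too far, because the Sample size section names attendance as the primary objective. Table 1 nevertheless places efficiency, time and cost under Primary, so the two sections need to be aligned.
- **A multiplicity rule may be in an analysis plan not shown.** It could be, and its absence from the article is not the complaint. An alpha split there would leave the printed 80% wrong: at 0.025 per contrast and 50 per arm, power is about 69-72% per contrast.

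**Conclusion.** The point holds and should be fixed. The stated 5% and 80% both apply only to each contrast taken alone. With success on either contrast, the two-sided type I error is about 9.6% at 50 per arm (4.8% for false superiority of SMS + Call over at least one arm). With success on both, power is about 69-72% at 50 per arm, or 74-77% if all 56 per arm are analysed.

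These figures assume the article's own rates, SMS + Call between 84.0% and 84.6%, independent subjects and uncorrected chi-square tests. The error rates take 59% attendance in all arms. The consequence is an unclear success criterion and a power figure not tied to it; the data to be collected are not affected.

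**What to change.** 1. Make attendance the sole primary outcome, in line with the Sample size section. Move the efficiency ratios, working time and cost to secondary in the Primary outcomes section and Table 1.
2. State the success rule for the two-versus-one hypothesis and restate power to match. Two options:
   - **Preferred: both contrasts.** SMS + Call must be significantly better than SMS only and than Call only, each at two-sided 0.05. No alpha split is needed. State power of about 69-72% with 50 per arm evaluable.
   - **If the sponsor means an average effect: one pooled test.** Compare Group 4 with Groups 2 and 3 combined at two-sided 0.05, with about 89-91% power at 50 v 100. Acknowledge that a positive result does not show superiority over each single reminder.

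**Cost.** Wording only, with no added participants. The article reports recruitment as ongoing, so the change can be recorded before the data are analysed. The downside is a less favourable stated power under the first option, or a weaker claim under the second. Restoring 80% joint power under the first option would need about 62-65 evaluable per arm by normal approximation, which is 69-73 per arm after 10% attrition (62/0.90 = 68.9; 65/0.90 = 72.2). This is not required for the fix.
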